### Randomization and Allocation

Randomization is carried out using a 1:1 allocation ratio through a computer-generated sequence, employing stratified block randomization to ensure balance between key co-variates.

Block randomization within strata works by first dividing participants into homogeneous subgroups (ie, strata) based on key baseline co-variates (eg, age). Within each stratum, participants are then randomized in small, fixed-size blocks to ensure that each treatment group is equally represented in every block. This dual-layered approach helps to maintain overall balance in treatment allocation across important co-variates (through stratification) while also preventing accidental imbalances due to random chance within each stratum (through blocking). It is particularly effective with a limited number of relevant predictors and in samples of small to moderate size, where simple randomization may lead to imbalance.^
44
^ In our case, we opted for stratification by age (<50 years vs ≥50 years), sex (male vs female), and geographical area (Southern vs North-Eastern Switzerland), and use blocks of 4 to ensure consistent treatment balance within each stratum.

The random allocation sequence is generated by the investigator overseeing the Ticino study site, without involvement from external personnel. Randomization is conducted after the completion of participant recruitment and immediately prior to onboarding and initiation of the intervention phase. Because randomization occurs only after recruitment is finalized, no ongoing allocation sequence requires concealment, eliminating the potential for selection bias due to prior knowledge of group assignments.

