### Sample Size Calculation

We estimate the minimum sample size for a 2-arm, parallel-group superiority RCT with a continuous outcome and 1:1 allocation using the standard formula:

$$n=\frac{2\sigma^{2}{\left(Z_{\alpha /2}+Z_{\beta }\right)}^{2}}{\Delta^{2}}$$

where *n* is the required sample size per group, *σ* is the standard deviation of the outcome, ∆ is the expected difference (minimum clinically important difference) between groups, *Z_α/_*_2_ is the critical value for a 2-sided significance level (*α* = .05), and *Z_
_β_
_* is the critical value corresponding to 80% power.

To inform the parameters *σ* and ∆, we use empirical data from a previous observational study conducted by the REHEAT research team on a sample of 294 office workers in Canton Ticino (Southern Switzerland), monitored for 30 working days between February and April 2024.^
45
^ In that study, daily recovery was defined as the normalized difference between so-called “body battery levels” (a measure assessed by means of smartwatches) in the evening and at wake-up. A fixed-effects panel regression model is estimated, with recovery in body battery levels as the dependent variable and average daily temperature (from the Lugano MeteoSwiss station) as the main predictor, controlling for perceived health, weekday, and week number.

Due to the absence of days with average temperatures above 18^◦^C in that dataset, we extrapolate the expected effect of hot days by assuming a linear relationship between temperature and recovery. We use predicted average recovery values for moderate days (14°C-18°C, typical of June in Canton Ticino) as the baseline and compare them to predicted values at 25°C—the MeteoSwiss threshold for heat episodes.^
56
^ The resulting difference in recovery is used as the expected intervention effect (∆), under the assumption that the REHEAT strategy could fully mitigate the adverse impact of heat.

Although optimistic, this assumption is conservative in terms of sample size estimation: the effect size is derived from a lower-risk population (office workers) and under the assumption of linearity, whereas prior literature suggests that the impact of heat on health is often nonlinear and intensifies at higher temperatures.

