### Statistical Analysis Plan

The evaluation of the REHEAT heat adaptation strategy consider the following 4 areas: implementation and compliance, impact, heterogeneity, and satisfaction.

Implementation and compliance: descriptive statistics and inferential comparisons assess baseline equivalence between treatment and control group and participant compliance across relevant sociodemographic characteristics, work experience, health condition, and selected outcomes. App usage data is analyzed using frequency distributions and stratified analyses by age, sex, and location to ascertain user engagement with the app.Impact Analysis: The impact of the REHEAT strategy is first evaluated using an Intention-To-Treat (ITT) approach, which yields the most reliable estimates for real-world interventions by preserving the benefits of randomization. In parallel, Local Average Treatment Effects (LATE) are estimated to assess the intervention’s effects at varying levels of participants’ potential heat exposure and compliance. ITT analyses are conducted at the individual level. The effects of REHEAT on the primary outcomes—measured at on-boarding and off-boarding—as well as on those monitored throughout the summer, are estimated using random-intercept mixed-effects models. By accounting for within-subject correlations over time, this approach supports a robust analysis of longitudinal data. LATE estimates on primary outcomes are derived using instrumental variable generalized linear mixed models (IV-GLMM), with MeteoSwiss weather data and REHEAT app usage serving as instruments. Specifically, passively recorded data on the frequency of use of the app’s features over time are used as a proxy for participants’ compliance with the intervention. These models control for randomization strata and blocks, as well as a set of time-invariant and time-varying co-variates deemed theoretically or empirically relevant. Because heat effects vary across time, cumulative exposure, and acclimatization,^57,58^ temporal factors are explicitly controlled in the analyses. Exposure to heat is modeled using distributed lag models to capture both immediate and delayed effects of temperature and humidex across pre-specified lag periods. Mixed-effects models include calendar-week splines, random slopes for time, and adjustments for survey date and recent mean temperature to account for differences in measurement timing and seasonal acclimatization.^
59

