^ Potential time-invariant characteristics of the respondents (eg, years of experience in home care, chronic conditions), and time-varying confounding due to intermediate variables (eg, workload changes, night shifts) are also addressed in sensitivity analyses.

Effect Heterogeneity: interaction terms are included in multilevel models to explore differences in outcomes by sex, age, geographical region, and time-related factors. Separate models assess moderation effects by these variables in both ITT and LATE frameworks. Random intercept multilevel regression techniques are used to model hierarchical longitudinal data that violate the independence assumption (ie, repeatedly measured continuous outcomes). The heterogeneity of heat episode effects are estimated by multiple-interaction models in which interaction terms between the heat episode, the participant’s area of work, age, and sex are estimated. To capture temporal heterogeneity, additional interaction terms assess whether the REHEAT strategy differentially mitigates heat effects over the course of the summer. Treatment-by-time interactions, such as calendar week, cumulative heat exposure, or time since onboarding, are used to examine whether intervention effects vary due to seasonal acclimatization or repeated exposure.^
59
^ Flexible calendar-week splines and random slopes for time allow for individual adaptation trajectories and evolving heat vulnerability. These analyses determine whether the REHEAT strategy effectively addresses the diverse and changing needs of home care workers operating in different areas of Switzerland, who are exposed to different climatic, organizational and contextual conditions, while also estimating average conditional treatment effects across demographic and temporal dimensions.

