## Results

At the time of submission, recruitment had been successfully completed, with a total of 350 participants enrolled as planned. This number falls within the target range defined to ensure adequate statistical power and account for the applied safety margin. The intervention and data collection phases are ongoing, involving the continuous acquisition of physiological, environmental, and self-reported data through the REHEAT app and wearable sensors. Data quality checks and system monitoring procedures are currently in place to ensure completeness and reliability. No outcome data have yet been accessed or analyzed at this stage, and qualitative interviews with a sub-sample of participants are scheduled for Autumn 2025.

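### The random-intercept and random-slope models named for the daily outcomes do not carry day-to-day serial correlation, so a treatment-by-calendar-week test fitted flexibly with only these random effects would reject too often

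*Protocol article*

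**What the plan says.** All references are to the protocol article, section Statistical Analysis Plan, unless stated.

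- **Impact Analysis.** Outcomes monitored through the summer are analysed with random-intercept mixed models. The justification is: "By accounting for within-subject correlations over time, this approach supports a robust analysis of longitudinal data". Calendar-week splines and random slopes for time are added further on.
- **Effect Heterogeneity.** The dependence is dealt with again in these words: "Random intercept multilevel regression techniques are used to model hierarchical longitudinal data that violate the independence assumption". The tests at issue are then announced: "Treatment-by-time interactions, such as calendar week, cumulative heat exposure, or time since onboarding, are used to examine whether intervention effects vary". On individual change the text says: "Flexible calendar-week splines and random slopes for time allow for individual adaptation trajectories".
- **Outcomes, Table 1.** Every primary outcome has a daily time frame. Sleep and health also have pre- and post-intervention measurements.

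The article names neither a residual correlation structure nor a participant-clustered variance. It does not give the form of the treatment-by-week term (linear, spline or categories).

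**The concern.** A random intercept gives any two days from one person the same correlation, whether they are one day or two months apart. A random linear slope lets people drift apart along straight lines. Heart-rate measures, sleep, affect and recovery on consecutive days can be more alike than either term allows, and that excess stays in the residual.

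The consequence depends on the contrast. A flexible treatment-by-week term compares runs of neighbouring days. Positive serial correlation makes averages over such runs more variable than the model believes, so the standard errors are too small. A treatment effect that is constant over the summer could then be reported as waning, growing or varying by week. Whether it changes with acclimatization or repeated exposure is something the heterogeneity analysis sets out to examine.

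**Working it through.** **Plan's own figure.** The article states no error rate for these tests. The only significance level is in Sample Size Calculation, where the Z value "is the critical value for a 2-sided significance level" of .05. I take 5% as the nominal level. Sigma and delta are not given, so the sample size cannot be rebuilt. The point does not depend on it, because the error rates below are large-sample values.

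**Inputs from the article.** Daily recording (Table 1); random intercept and random slope for time (Statistical Analysis Plan); 350 participants (Results), allocated 1:1 (Randomization and Allocation).

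**Assumed inputs.** 90 complete days per person; half the variance between persons; residual lag-1 correlation ρ from 0 to 0.5; a 5-df week basis, leaving 3 non-linear treatment-by-week terms tested jointly.

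**Method.**
1. True covariance S = random intercept (0.5) + random slope (SD 0.2 per SD of time) + within-person error (0.5). The error is AR(1), or half AR(1) and half white noise.
2. Working covariance V = random intercept + random linear slope + independent residual, with the components that best fit S (minimum of log|V| + tr(V⁻¹S)).
3. Model-based variance A = (X′V⁻¹X)⁻¹. True variance R = A(X′V⁻¹SV⁻¹X)A.
4. The rejection rate of the 3-df Wald test follows from the eigenvalues of A⁻¹R for the 3 terms, compared with the χ² critical value 7.815.

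**Results, random intercept plus linear slope, 3 non-linear terms.**

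| ρ | SE too small by factor (pure AR(1)) | False positives, pure AR(1) | False positives, half white noise |
|---|---|---|---|
| 0 | 1.00 | 5% | 5% |
| 0.1 | 1.10 | 9% | 7% |
| 0.2 | 1.22 | 15% | 10% |
| 0.3 | 1.35 | 23% | 13% |
| 0.5 | 1.71 | 43% | 25% |

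Repeat calculations agree to within about one to two percentage points.

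**Hand check.** For a slow contrast the variance ratio is close to (1+ρ)/(1−ρ). At ρ = 0.3 this is 1.3/0.7 = 1.86, and √1.86 = 1.36, against 1.35 in the table. The test then behaves like P(χ²₃ > 7.815/1.86 = 4.20), which is about 24%, against 23%.

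**Other forms of the test** (91 days, pure AR(1), ρ = 0.1 / 0.2 / 0.3 / 0.5).

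| Test | Random intercept only | With random linear slope |
|---|---|---|
| Linear treatment-by-week | 7.7 / 10.9 / 14.8 / 25.3% | about 5.0% throughout |
| 4-df spline | 9.8 / 16.8 / 26.2 / 50.3% | 8.5 / 13.7 / 20.9 / 40.3% |
| Week as categories | 12.4 / 24.7 / 40.7 / 73.3% | 11.7 / 22.7 / 37.4 / 69.5% |
| Time-constant treatment effect | 5.0% | 5.0% |

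**Simulation check.** 150 simulated trials (120 people, 91 days, ρ = 0.3, spline), fitted as mixed models, rejected 21% of the time with a random intercept and 18% with a random slope added. Simulation error is about 3 points.

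**The case against.** - **A linear slope is an inference.** The text never says linear, and the sentence on individual adaptation trajectories could mean person-level spline coefficients. With random coefficients on the same basis as the tested terms, the 3-df test rejects at 4.9 to 5.2% for ρ from 0.1 to 0.5, with no further remedy. This stands: the inflation belongs to the other reading.
- **The tested form is not stated.** Nothing says that treatment is interacted with the spline. A linear treatment-by-week or time-since-onboarding test keeps 5% once the random slope is in. This stands too, so it would be wrong to infer that every treatment-by-time test is inflated.
- **The correlation is assumed.** At 0.1, or with much day-level noise, the excess is modest (7 to 9%). Onboarding in June or July and missing days shorten or thin the series. With weekly instead of daily records the largest rate found was 7.7%. In the other direction, the temporal smoothing planned for missing physiological data would add short-range correlation.
- **This is a condensed article.** A residual structure or clustered variance may be set in a fuller plan that is not shown, and the article does not say that residuals are independent. Its silence is therefore no finding. What remains is what it does say: it presents random intercepts as accounting for correlation over time and calls the analysis robust on that ground. For daily series that claim is too strong, whatever a fuller plan adds.
- **The tests are exploratory.** Change over the summer is in neither the Objectives nor the Hypotheses. This limits the consequence but does not remove it.

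**Conclusion.** The point holds conditionally. The stated remedy for dependence does not cover serial correlation between days. If the treatment-by-calendar-week interaction is flexible and only a random intercept and a random linear slope are used, its tests are anti-conservative. The rate is about 9 to 43% for lag-1 correlation 0.1 to 0.5, or about 7 to 25% if half the within-person variance is white noise. These figures rest on the assumed 90 complete days, half the variance between persons and 3 non-linear terms. With a random intercept alone, the linear test is inflated as well.

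A reader might infer that the trial's main conclusion is compromised, or that false positives several times the nominal rate are certain. The documents support neither. The time-constant intention-to-treat effect keeps 5% in every scenario, and the article gives neither the correlation nor the form of the interaction. At stake is the credibility of any reported change in the effect over the summer.

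**What to change.** 1. For the daily-outcome models, base the treatment-by-time tests on participant-clustered, small-sample-corrected standard errors, or add a continuous-time AR(1) residual within participant, which allows for gaps. Clustering does not depend on the serial form being right, and about 350 participants are ample clusters.
2. Reword the Impact Analysis sentence so that it no longer says random intercepts alone account for correlation over time. Make the matching change in Effect Heterogeneity.

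**Cost.** A model option in software the article already names (Stata, R) and a sentence or two of text. Fitting is slower, and intervals for the flexible time interactions widen, by roughly the factors in the table (1.10 to 1.71 under the pure AR(1) assumptions). The Results section says no outcome data had been accessed at submission; if that still holds, the change can be made without suspicion of a data-driven choice.

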The estimation of potential rather than actual heat exposure may also introduce non-differential measurement error, attenuating observed effects. In this study, daily potential exposure was estimated using meteorological data from each participant’s local administrative unit, within-subject variations were analyzed over time, and time- and weather-related covariates controlled for. To our knowledge, no wearable devices currently exist that can reliably measure environmental temperature and humidity over extended periods for homecare workers during and outside work. Future studies will require such tools to capture real heat exposure, improving exposure assessment and strengthening causal inference without relying on self-reported data.

Finally, external validity may be limited to the Swiss context, as the intervention’s effectiveness could be influenced by substantial heterogeneity across geographical areas. Differences in local infrastructure, organizational practices, and cultural contexts, as well as variations in prior heat exposure and climate habituation, may all shape both risk perception and responses to the intervention. Recognizing these sources of heterogeneity is important for interpreting the results and for planning future studies in different settings or populations to generalize them.

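### The heat models name no worker-level heat slope and no unit-by-day term, so intervals for heat, heat-by-area and arm-by-heat effects can be too narrow

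*Protocol article*

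**What the plan says.** All the model statements are in the protocol article, Methods, Statistical Analysis Plan.

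- **Impact Analysis.** Effects on the primary outcomes "are estimated using random-intercept mixed-effects models". The stated reason is the repeated measurement of each person: "By accounting for within-subject correlations over time", the analysis is said to be robust. Further terms are then listed: "Mixed-effects models include calendar-week splines, random slopes for time, and adjustments for survey date and recent mean temperature". Heat itself enters through distributed lags of temperature and humidex.
- **Effect Heterogeneity.** The error structure is repeated: "Random intercept multilevel regression techniques are used to model hierarchical longitudinal data that violate the independence assumption". Heat is then interacted with worker characteristics: "The heterogeneity of heat episode effects are estimated by multiple-interaction models in which interaction terms between the heat episode", area of work, age and sex are fitted. For the intervention, "additional interaction terms assess whether the REHEAT strategy differentially mitigates heat effects over the course of the summer". On between-worker differences the text says: "Flexible calendar-week splines and random slopes for time allow for individual adaptation trajectories and evolving heat vulnerability".
- **Discussion.** On exposure, "daily potential exposure was estimated using meteorological data" for the local administrative unit of each participant.
- **Table 1.** All six primary outcomes have a daily time frame centred on comparing baseline with heatwave periods.

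Neither section names a random slope for heat, a day, unit-by-day or area-by-day effect, or a clustered variance.

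**The concern.** The named random terms all sit at the participant level, and the only random slope is on time. Heat varies at a different level. It is a property of a place on a day, shared by every worker in a local unit and correlated between neighbouring units.

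1. **Shared days.** Anything else that happens in a place on a day (a holiday, a workload surge, weather not captured by the covariates) moves many workers together. A model with participant effects only treats each worker on a hot day as separate evidence. For heat and heat-by-area effects, the real replication is the number of hot days and episodes in one summer. A smooth spline over weeks does not absorb day-to-day shocks.
2. **Heat response.** A slope on time lets workers drift apart over the summer. It does not let them differ in how they respond to a hot day, so the sentence about evolving heat vulnerability claims more than the model delivers. Arm by heat episode is then tested as if all workers in an arm had the same heat response apart from the covariates. Yet the Hypotheses expect benefit to differ by age and sex, and the Discussion expects differences by prior exposure and habituation.

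The second problem reaches the randomised question, because Table 1 puts the contrast between baseline and heatwave days at the centre of the daily primary outcomes.

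**Working it through.** **No figure to reproduce.** The article gives no standard error, day variance, heat-slope variance or expected number of heat days. Everything below shows a range over assumed values.

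**Inputs from the article:** 350 participants, 1:1 allocation, two study areas, one summer, two-sided 5% level.

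**Assumed:** 175 workers per area and 175 per arm; 92 complete days; residual SD 1; about 16% of days hot; area temperatures autocorrelated (0.8) and sharing 60% of their variance; day shocks autocorrelated (0.3), half of their variance common to both areas; all true effects zero. The fitted model removes a participant intercept and time slope, and includes a calendar-week spline, heat, heat-by-area and heat-by-arm. Each setting had 600 runs, and runs with under 5% heat days in an area were dropped (about 500 to 535 kept).

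**Control.** With no day shocks and no heat-slope variation, true SE / model SE was 0.98 to 1.01 and rejection was 4% to 6%. The described model is valid in that case.

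**Step 1: shared day shocks.** Let m workers share a shock whose variance is a fraction v of the within-person variance. Then, roughly, true SE / model SE = √(1 + m·v). With m = 350/2 = 175:

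| v | √(1 + 175v) | Simulated, heat | Simulated, heat × area | Rejection, heat × area | Simulated, heat × arm |
|---|---|---|---|---|---|
| 0.5% | 1.37 | 1.32 | 1.44 | 16% | 1.02 |
| 1% | 1.66 | 1.65 | 1.66 | 24% | 1.00 |
| 2% | 2.12 | 1.86 | 2.14 | 35% | 1.00 |
| 5% | 3.12 | 2.88 | 2.96 | 50% | 1.04 |

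The heat-by-arm rejection rate stays at 4% to 5%, because both arms share the shock and it cancels.

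**Step 2: milder settings, closer to the text.**

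- *Heat differs between local units* (ten per area, two degrees of spread), v = 2%: ratios 1.43 to 1.59 for heat and 1.51 to 1.72 for heat-by-area.
- *Survey date entered as a factor* (200 runs, 160 to 173 kept). A shock wholly common to both areas disappears: 0.98 and 1.01. With half of it area-specific, the ratios are 1.49 (heat) and 1.58 (heat-by-area) at v = 1%, and 1.67 and 1.78 at v = 2%.

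The local-unit runs gave 1.09 to 1.10 for heat-by-arm, but their layout placed each unit wholly in one arm. Rerun with arms randomised within area, as in the trial, the ratio was 1.01 to 1.02 and rejection 4% to 5%.

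**Step 3: missing heat slope.** Let S be one worker's sum of squares of the heat indicator after removing intercept and time, and τ the SD of heat response between workers. The variance of the arm-by-heat estimate is 4(σ²/S + τ²)/350. The described model sets τ = 0, so true SE / model SE = √(1 + τ²S/σ²). The simulated model SE of 0.0323 implies S = 4/(350 × 0.0323²) = 10.95. Rejection is 2[1 − Φ(1.96/ratio)].

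| τ (residual SDs) | Formula ratio | Simulated ratio | Formula rejection | Simulated rejection |
|---|---|---|---|---|
| 0.1 | 1.05 | 1.06 | 6% | 6% |
| 0.2 | 1.20 | 1.19 | 10% | 10% |
| 0.3 | 1.41 | 1.43 | 16% | 16% |
| 0.5 | 1.93 | 1.94 | 31% | 31% |

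A date factor does not help here: the ratio at τ = 0.3 is still 1.43. The missing slope also touches heat and heat-by-area (1.45 and 1.40 at τ = 0.3).

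**The case against.** Several stronger readings are tempting, and the documents do not support them.

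- **That the listed random terms are the only ones.** The article says what the models include. It does not say that nothing else enters, or that model-based standard errors will be used. A fuller plan may add terms. This stands, so the point is about the structure the article names. It is not mere silence, though: the article does state an error structure, justifies it by within-subject correlation, and credits the time slope with something it cannot do.
- **That everyone in a study area has the same heat value.** The Discussion assigns exposure by local administrative unit. This stands, and it shrinks the first problem without removing it (Step 2).
- **That the standard errors are bound to be far too small.** No variance component is given. Survey date, recent temperature, distributed lags and time-varying covariates may absorb part of the day shocks. If survey date is a factor and all shocks are common to both areas, the first problem vanishes.
- **That shared days create false-positive benefit of the app.** They do not. The shocks cancel between arms, so neither the arm main effect nor the arm-by-heat contrast is affected. The high rejection rates in Step 1 belong to observational contrasts, in analyses that the article introduces as exploring differences.

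It can also be said that the heat-slope problem is modest. At τ = 0.1 there is almost no inflation. For treatment by cumulative heat, which correlated about 0.95 with calendar time in a similar simulation, the planned time slope absorbs much of the variation: rejection was 6%, 8% and 13% at slope SDs of 0.1, 0.2 and 0.3 per SD of cumulative heat, against 15%, 39% and 48% with an intercept only. That is a fair limit. It does not cover the acute contrast between hot and other days, on which Table 1 focuses.

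**Conclusion.** The concern holds as two separate and conditional statements.

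1. Heat and heat-by-area standard errors are too small whenever unit- or area-specific day correlation remains after adjustment. The true value is about 1.3 to 3 times the model's for assumed area-by-day shocks of 0.5% to 5% of within-person variance. At a 2% shock it is about 1.4 to 1.8 times if heat varies between local units, or if survey date is a factor and half of the shock is area-specific.
2. The arm-by-heat-episode interval is too narrow if heat response varies between workers, with rejection of about 6%, 10% and 16% at assumed slope SDs of 0.1, 0.2 and 0.3.

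The sizes depend on variances that the article does not report. The direction does not: the named terms can only understate uncertainty if either source of variation exists. The intention-to-treat main effect of arm is not in question. The change should be made, and since the Results section says no outcome data had been accessed at submission, it could still be pre-specified then.

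**What to change.** - In every model with a heat or arm-by-heat term, add a participant random slope for heat, and correct the sentence that lets the time slope stand in for differing heat vulnerability.
- For heat and heat-by-area terms, also add a local-unit-by-day or area-by-day random effect, or use two-way clustered variance by participant and area-day.
- State whether survey date enters as a factor or a trend, since this decides how much of the shared-day problem is left.
- Report the number of heat days and distinct heat episodes per region beside the results, so that readers can see how much replication the heat contrasts have.

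The cost is two further variance components in mixed models that are already planned. Intervals become wider for heat and heat-by-area effects and modestly wider for arm by heat. No new data are needed.
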